## Abstract

**Background:**

Cerebral palsy (CP) is the most common developmental motor disorder in children. Individuals with CP demonstrate abnormal muscle tone and motor control. Within the population of children with CP, between 4% and 17% present dystonic symptoms that may manifest as large errors in movement tasks, high variability in movement trajectories, and undesired movements at rest. These symptoms of dystonia typically worsen with physical intervention exercises.

**Objective:**

The aim of this study is to establish the effect of haptic feedback in a virtual reality (VR) game intervention on movement outcomes of children with dystonic CP.

**Methods:**

The protocol describes a randomized controlled trial that uses a VR game-based intervention incorporating fully automated robotic haptic feedback. The study consists of face-to-face assessments of movement before, after, and 1 month following the completion of the 6-session game-based intervention. Children with dystonic CP, aged between 7 and 17 years, will be recruited for this study through posted fliers and laboratory websites along with a group of typically developing (TD) children in the same age range. We anticipate to recruit a total of 68 participants, 34 each with CP and TD. Both groups of children will be randomly allocated into an intervention or control group using a blocked randomization method. The primary outcome measure will be the smoothness index of the interaction force with the robot and of the accelerometry signals of sensors placed on the upper limb segments. Secondary outcomes include a battery of clinical tests and a quantitative measure of spasticity. Assessors administering clinical measures will be blinded. All sessions will be administered on-site by research personnel.

**Results:**

The trial has not started and is pending local institutional review board approval.

**Conclusions:**

Movement outcomes will be examined for changes in muscle activation and clinical measures in children with dystonic CP and TD children. Paired *t* tests will be conducted on movement outcomes for both groups of children independently. Positive and negative results will be reported and addressed.

**Trial Registration:**

ClinicalTrials.gov NCT03744884; https://clinicaltrials.gov/ct2/show/NCT03744884 (Archived by WebCite at http://www.webcitation.org/74RSvmbZP)

**International Registered Report Identifier (IRRID):**

PRR1-10.2196/11470

## Introduction

### Background

Cerebral palsy (CP) is the most common developmental motor disorder in children, present in 3.6 of every 1000 live births in the United States [1]. Individuals with CP demonstrate abnormal muscle tone and motor control that contribute to impaired postural control and movement coordination that compromise health [2,3]. CP is considered a static encephalopathy; there is no known cure, and the physical impairments present at early age tend to worsen with time [4].

Between 4% and 17% of children with CP present dystonic symptoms as the predominant motor impairment [5]. Dystonia is typically characterized by involuntary muscle activity that may be sustained or intermittent, thereby causing abnormal postures or movements that can be described as trembling, writhing, or contouring [6-8]. These abnormal movements are often present during attempted voluntary movement and can worsen when this movement is sustained [7].

Approximately 70% of children with CP present spastic symptoms. Spasticity manifests as (1) increased resistance to external muscle stretch that varies with flexion or extension and/or (2) resistance that quickly rises past a certain joint angle position or velocity [6,7]. Dystonia and spasticity often manifest in the same child with CP [5,7,9].

The main goals of rehabilitation in CP include promoting function while decreasing the risk for skeletal deformity and muscular atrophy later in life [10-14]. Rehabilitative therapies for CP most commonly include orthopedic surgery, botulinum toxin injections, and physical therapy (PT). PT interventions consist of intensive stretching and strengthening exercises and, more recently, high dosage robotic training [10-14]. However, dystonia worsens with PT and is often “refractory to treatment” [15]. Management of dystonia typically involves oral medication that produces little improvement and may have adverse side effects [16]. It has been recently shown that deep brain stimulation provides only moderate benefits in some patients with dystonia and none in others [16-21]. In individuals with combined spasticity and dystonia, physical interventions that improve spastic symptoms cause worsening of dystonic symptoms [7].

This worsening of dystonic symptoms is thought to be caused by abnormal signal-dependent noise modulated by the central nervous system [15]. With this in mind, we consider a low-magnitude (30% ± 10% maximum voluntary contraction) isometric force task intervention to limit signal-dependent noise that is characteristic of dystonia while minimizing movement- related sensory feedback. In addition, the intervention is designed as a virtual reality (VR) game aiming to stimulate motivation and attention as part of the rehabilitation strategy. Motivation and attention have been recognized by the National Institutes of Health Taskforce on Neuroplasticity for Clinical Applications as key for neuroplasticity during rehabilitation [8].

We hypothesize that training children with dystonic CP to match force direction targets at low magnitudes of isometric force with real-time feedback in a low dimensional space rendered in VR will improve quantitative and clinical movement outcome measures.

### Choice of Comparator

Children aged 7 to 17 years with dystonic CP and a group of typically developing (TD) children in the same age range will be recruited for the study. The CP and TD groups will be randomly assigned to an intervention or no-intervention (control) group. The control groups will be assessed in the same schedule as the intervention groups. Participants will continue with their regular PT schedule and continue their typical exercise regimen as applicable.

### Trial Design

We will conduct paired *t* tests on movement outcomes for the CP and TD groups independently. In case of non-normality, nonparametric techniques will be used. Differences before and after as well as before and follow-up will be obtained on the primary outcome measure: smoothness of movement. Differences will also be calculated on secondary outcomes for exploratory purposes. The primary outcome measure will be the smoothness index of the accelerometry signals of sensors placed on the upper limb segments. Secondary outcomes include the interaction force with the robot and a battery of clinical tests and a quantitative measure of spasticity. The study is powered for the main outcome. The desired allocation will be 1:1, with 1 participant in the control group for every participant in the intervention group for both CP and TD participants.

In the application presented here, the VR environment follows a prescribed remapping based on principal component analysis of force data generated from people with typical movement control [22,23]. Participants will, therefore, be asked to produce efforts in directions of high variance that are associated with performance of typically developed adults.

This intervention will not be incorporated into a broader health care program at this time.

### Objective

The primary objective was to establish the effect of a VR game-based force-direction training intervention on movement outcomes of children with dystonic CP using robotic feedback.

## Methods

### Study Setting

All procedures will take place at 2 sites: the Neuroscience of Dance in Health and Disability laboratory located at the University of Illinois at Urbana-Champaign (UIUC) or the Children’s Hospital of Illinois/OSF Saint Francis Medical Center. Both sites are located in Illinois, United States and are in the urban counties of Champaign and Peoria, respectively. The ethno-racial composition of the state of Illinois for the population younger than 18 years is approximately 66% white, 24% Hispanic, 16% black, 13% other, and 5% Asian. Expected total recruitment is 68 participants (Table 1) [24].

### Eligibility Criteria

The inclusion criteria are shown in Textbox 1. The exclusion criteria included not meeting all inclusion criteria.

### Interventions

All potential participants will be assessed to verify that inclusion and exclusion criteria are met during baseline assessments before being allocated into an intervention or control group. Participants in the control group will be assessed at a study site approximately 6 times, each lasting a maximum of 1.5 hours. The assessments will take place over the course of 6 to 7 weeks; there will be baseline assessments, postassessments, and 1-month follow-up assessments. Participants will attend a total of approximately 9 hours for the assessments involved in the study. All participants will be asked to continue typical PT or exercise routines outside of the study. A parent or guardian will be requested to stay in the research room at all times to further ensure participant safety and comfort.

Participants randomly allocated into the game-like intervention will participate in 6 training sessions, of up to 1 hour in duration, in addition to assessments for a total of 12 sessions. The intervention will occur over a 1- to 2-week period depending on schedule accommodations. Total participation time for intervention groups is estimated at 15 hours. Participants will play the VR game in which they will produce isometric efforts against the robot-force transducer unit that is programmed to resist their effort with a static torque control mode. The active game play time will be anywhere between 10 and 30 min depending on user preference. The source code and VR game will be available upon request.

**Table 1 table1:** Allocation by performance site. It is expected that most participants will be tested at the Peoria location.

Performance site	Male (n=34), n (%)	Female (n=34), n (%)	Total (N=68), n (%)
Neuroscience of Dance in Health and Disability Laboratory, Kinesiology and Community Health, and UIUC^a^	12 (35)	12 (35)	24 (35)
Children’s Hospital of Illinois/OSF Saint Francis Medical Center, Peoria, Illinois	22 (65)	22 (65)	44 (65)

^a^UIUC: University of Illinois at Urbana-Champaign.

Inclusion criteria.Aged between 7 and 17 yearsDiagnosis with dystonic cerebral palsy (CP), for participants with CP, or have no neuromuscular conditions, for typically developing participantsMild to no difficulty understanding conversations compared with others of the same ageCommunicate age appropriately or with some difficulty, but a new listener can understandNo uncorrected visionHearing without the need of a hearing aidNo other neural, neuromuscular, or musculoskeletal conditionsNo history of surgical procedures within 6 months before enrollment in the studyParticipation in stable school and/or private physical or occupational therapy with a frequency no greater than 2 sessions per week for cerebral palsy groupsNo changes in medication for the 6 months before enrollment in the studyMedically stableNo other concurrent illnessReceived no Botox treatment within 3 months previous to the initiation of the studyNo use of cardiac pacemakers, hearing aids, or another electronic implanted deviceAbsence of allergy to silver or skin adhesivesNo history of seizuresManual Ability Classification System score I-III

**Figure 1 figure1:**

Projection into virtual reality (VR) space. The vector x in VR space is the projection of the signal vector b of n=6 force and torque signals, by the principal components matrix A.

The robot-force transducer unit consists of a 6-dimensional force and torque transducer (ATI-Nano 25, ATI Industrial Automation, North Carolina) mounted onto the end-effector of a 5 degree of freedom robotic arm (KUKA Roboter gmbh, Augsburg, Germany) that is fixed to a table. The end of the robotic arm is positioned in 5 points within the reach space of the upper limb in a vertical plane by custom software (Microsoft Visual Studio Professional 2015, Redmond, Washington). Participants will apply force to the sensor via a comfortable gripper and will receive real-time feedback on the forces and torques exerted by the hand against the robot. Feedback will be mapped onto a space displayed on a flat monitor (refresh rate: 60 Hz) or VR head mounted display (Oculus Rift ConsumerVersion1, refresh rate: 90 Hz, Oculus, Menlo Park, California).

The force and torque signals will be remapped into the VR game using the principal component analysis matrix of the average set forces and torques generated against the robot from pre-existing data of healthy adults, such that if b is the vector of n=6 force and torque signals and A is the principal components matrix then x is the projection in the VR space as shown in Figure 1. In the simplest level of the game, only the first row of the principal components matrix (n=1) is projected into the game. Following levels increase in difficulty as rows of the matrix are incorporated in the mapping (n=2, 3, …, 6).

Participants will be allowed to rest as desired between efforts that will be at 30% ± 10% of the maximal voluntary contraction for each participant. The custom game (Unity, Unity Technologies SF, San Francisco, California) requires the participants to match remapped lower-dimensional force targets that are displayed as ships in a space exploration game. A total of 14 force and torque coordinates will need to be matched, 5 times, at the 5 robot positions, in spaces of reduced dimensions ranging from 1 to 6. The game increases in difficulty (number of matching dimensions) as the participant matches the targets successfully. Participants may choose to use a screen or VR headset to play the game according to their preference. VR sessions will be limited to 30 min for each session; the remainder of the hour will be used for setup purposes and administration of the maximum voluntary muscle contractions if surface electromyography (sEMG) will be used during the session. Muscle activity will be recorded with up to 16 wireless sEMG sensors (Trigno, Delsys, Massachusetts) that are placed bilaterally on the following muscles: middle deltoid, pectoralis major, anterior deltoid, latissimus dorsi, biceps brachii, triceps brachii lateralis, flexor carpi radialis, and extensor carpi radialis.

Participants will be able to stop participating at any time without consequence. If a child has a first seizure during the study, the inclusion and exclusion criteria will no longer be met, and participation in the study will be terminated. A procedural checklist will be followed during experiments.

### Outcomes

All participants will be assessed for outcome measures at a site using sEMG sensors embedded with inertial measurement units (ATI-Nano 25, ATI Industrial Automation, North Carolina) and the robot-force transducer unit. All assessments and measurements are noninvasive and involve minimum risk to the participants. The accelerometry data will be used to assess smoothness of movement during the execution of a prescribed movement and measures muscle activation patterns during assessments involving the robot-force transducer unit used to measure force and torque outputs within the reachable space of the upper limbs of the participant. In addition, the robot is programmed to produce a path of zero resistance, within the reachable space, that provides haptic feedback perpendicular to the path. For assessing children with CP, we will collect clinical and quantitative measures of upper limb range of motion, motor function, dystonia, and spasticity. The outcome measures will be obtained before, after the intervention, and at 1-month follow-up (Textbox 2).

Assessments 1 to 4 are standard clinical questionnaires and tests. Assessment 5 is a quantitative test of spasticity based on sEMG recordings and angle velocity of a joint by manual manipulation.

Assessment 6 involves the robot, force sensor, and sEMG. A predetermined zero-force path has been programmed by the research team to allow the robot to move through straight lines connected to 5 points on a vertical plane. These positions coincide with the 5 positions of the training intervention, resting in a reachable rhombus-like configuration. The participants will attempt to find and move along a zero-force path. The force transducer will measure the forces exerted by the participant as they do so. This task will be limited to a 7-min period or until the task is complete.

Measured outcomes. Measures for all participants (ie, listed from 6 to 10 will be done for all participants). The remaining articles are outcome measures for participants with cerebral palsy, that is, these will be specific to participants with cerebral palsy.Dyskinesia Impairment ScaleSelective Control of the Upper Extremity ScaleQuality of Upper Extremity Skills TestTardieu TestMontreal Spasticity Rating TestZero-Force Channel AssessmentSurface electromyography and accelerometryForces and torques against force sensorWorld Health Organization Disability Assessment Schedule 2 Children and YouthQualitative Feedback Module

Assessment 7 will be used as necessary during assessments and on the first and last day of gameplay. Accelerometry and sEMG data will be collected during the execution of a first *port de bras*. The first *port de bras* will follow the format from the Royal Academy of Dance as demonstrated (Figure 2). Accelerometry data will be integrated to calculate the smoothness index on the velocity profile of the trajectories [25]. Data will be analyzed for changes in muscle activity patterns and smoothness of movement. The sEMG data will also be acquired for maximum voluntary efforts.

Assessment 8 measures force and torque inputs using the force and torque sensor that is mounted on the end-effector of the robot. A maximum voluntary effort will be made by the participant’s dominant arm; the sensor will be mounted to a sturdy table for this task. The subject will be asked to push and pull along cardinal directions to determine the maximum force output that will be used to customize sensitivity subsequent efforts for each participant. Participants will also be assessed with the force sensor in 14 different directions at 30% ± 10% of the maximal force.

Assessment 9 is the World Health Organization Disability Assessment Schedule II-Children and Youth (WHODAS II-CY) that characterizes the children’s level of disability. This measure will only be used for population demographic purposes.

Assessment 10 will be the qualitative feedback module, which will provide qualitative feedback on participants’ experiences.

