**Figure 2 figure2:**
[figure not shown]
Royal Academy of Dance first port de bras. From left to right: en bas, first position, second position, and en bas. Participants will be asked to move through these positions during assessment 7 to measure muscle activity patterns and smoothness of movement.

**Table 2 table2:** Full study timeline. Experiment tasks are divided into weeks.

Time (weeks)	1	2	3	4	5	6	7	8	9 to 14	15 to 20
Recruitment and enrollment	✓^a^	✓	—^b^	—	—	—	—	—	—	—
Baseline assessments	✓	✓	—	—	—	—	—	—	—	—
Intervention period	—	✓	✓	—	—	—	—	—	—	—
Postassessments	—	✓	✓	—	—	—	—	—	—	—
1-month follow-up	—	—	—	—	—	✓	✓	—	—	—
Data processing	—	—	✓	✓	✓	✓	✓	✓	✓	—
Data analysis	—	—	✓	✓	✓	✓	✓	✓	✓	✓

^a^✓ corresponds to times when activity occurs.

^b^Empty cells indicate times when activity is not expected to occur.

**Table 3 table3:** Possible schedule 1. Interventions in this schedule will take place over a period of 2 weeks with days between. Assessments will take place over 2 days. This schedule is subject to change based on the participants’ availability.

Time (weeks)	1	2	3	4	5	6	7
Saturday	Assess	—^a^	Assess	—	—	—	Assess
Sunday	Assess	—	Assess	—	—	—	—
Monday	Game	Game	—	—	—	—	—
Tuesday	—	—	—	—	—	—	—
Wednesday	Game	Game	—	—	—	—	—
Thursday	—	—	—	—	—	—	—
Friday	Game	Game	—	—	—	Assess	—

^a^Empty cells indicate no activity.

**Table 4 table4:** Possible schedule 2. Interventions in this schedule will have no days between sessions. Assessments will take place over 2 days. This schedule is subject to change based on the participants’ availability.

Time (weeks)	1	2	3	4	5	6	7
Saturday	Assess	Game	—^a^	—	—	Assess	—
Sunday	Assess	Assess	—	—	—	Assess	—
Monday	Game	Assess	—	—	—	—	—
Tuesday	Game	—	—	—	—	—	—
Wednesday	Game	—	—	—	—	—	—
Thursday	Game	—	—	—	—	—	—
Friday	Game	—	—	—	—	—	—

^a^Empty cells indicate no activity.

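### The movement that yields the primary smoothness index is, on the plain reading, performed on two gameplay days that controls do not have, so practice on the outcome task is mixed with the training effect

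*Protocol article*

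**What the plan says.** Trial Design defines the primary outcome: "The primary outcome measure will be the smoothness index of the accelerometry signals of sensors placed on the upper limb segments". (The Abstract adds the smoothness of the interaction force with the robot; this point concerns the accelerometry index.)

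Outcomes explains where the index comes from. Under Assessment 7, "Accelerometry and sEMG data will be collected during the execution of a first" port de bras, and "Accelerometry data will be integrated to calculate the smoothness index on the velocity profile of the trajectories". The Figure 2 caption agrees: "Participants will be asked to move through these positions during assessment 7 to measure muscle activity patterns and smoothness of movement". One other activity is attached to Assessment 7, and it concerns sEMG only: "The sEMG data will also be acquired for maximum voluntary efforts".

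The timing is given in one sentence of Outcomes: "Assessment 7 will be used as necessary during assessments and on the first and last day of gameplay". Earlier in the same section, the outcome measures are said to be taken before the intervention, after it and 1 month later.

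Choice of Comparator makes the control condition no intervention and adds: "The control groups will be assessed in the same schedule as the intervention groups". Interventions gives controls about 6 assessment visits. Intervention children have 6 training sessions on top of their assessments, 12 sessions in all. The game itself consists of isometric efforts against the robot. The time in the training hour that is not game time goes to setting up and, when sEMG is used, to maximum contractions.

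**The concern.** The port de bras is a prescribed dance movement that many of these children may not know. Its smoothness could plausibly improve with repetition alone. If one arm repeats it on extra days between baseline and post-assessment, a difference in smoothness may reflect rehearsal of the test and not the force-direction training that the Objective sets out to evaluate.

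Randomisation does not protect against this, because the imbalance arises after allocation and is tied completely to the arm. No adjustment in the analysis can separate the two afterwards: every intervention child has the extra occasions and no control does.

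**Working it through.** **Step 1: what is done on gameplay days.** The sentence that places Assessment 7 on the first and last gameplay day is followed directly by the description of Assessment 7 as sEMG and accelerometry during a port de bras. The Figure 2 caption ties the same movement to Assessment 7. Gameplay is isometric, so play offers no movement trajectory from which this index could be computed. The plain reading is that the port de bras is performed on those two days.

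**Step 2: how many extra occasions.**
- Controls: about 6 visits, all assessments.
- Intervention: 6 assessments + 6 training sessions = 12.
- Intervention-only days with Assessment 7 scheduled: first and last gameplay day = 2.

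If Assessment 7 were used at every assessment visit, the totals would be at most 6 + 2 = 8 against 6. The number of visits per time point that include the task, and the repetitions per visit, are not stated. The firm figure is the difference of 2 scheduled occasions.

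**Step 3: when they fall.** The weeks in Tables 3 and 4 run Saturday to Friday.
- Table 3 ("Interventions in this schedule will take place over a period of 2 weeks with days between"): last game Friday of week 2, first post-assessment Saturday of week 3. Gap 1 day.
- Table 4: last game Saturday of week 2, first post-assessment Sunday of week 2. Gap 1 day.
- In both, the first game is the Monday of week 1, after baseline on Saturday and Sunday. Both extra occasions therefore lie between baseline and post-assessment.

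**Step 4: illustration of what a practice gain would do.** The documents give no practice effect, so the gain δ, in SDs of the change score, is an assumption. Sample Size gives 17 per group and 25% attrition: 17 × 0.75 = 12.75, about 13, as the protocol states. Training is taken to have no effect, and tests are two-sided at 5%.

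- Between-arm t test on change: df = 2n − 2, noncentrality = δ√(n/2). With n = 13 this is δ × 2.550, so 0.510, 0.765 and 1.275 for δ = 0.2, 0.3 and 0.5.
- Paired t test within the intervention arm: df = n − 1, noncentrality = δ√n. With n = 13 this is δ × 3.606, so 0.721, 1.082 and 1.803.

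| Assumed δ | Between-arm, n = 13 | Between-arm, n = 17 | Paired, n = 13 | Paired, n = 17 |
|---|---|---|---|---|
| 0 | 5.0% | 5.0% | 5.0% | 5.0% |
| 0.2 | 7.8% | 8.7% | 10.2% | 12.1% |
| 0.3 | 11.4% | 13.6% | 16.9% | 21.4% |
| 0.5 | 23.2% | 29.3% | 38.2% | 49.1% |

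Entries are the chance of a significant result from practice alone. The protocol names paired t tests for the CP and TD groups separately and no between-arm test, so the between-arm columns are not error rates of a stated analysis.

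**The case against.** The strongest reply is that no sentence says outright that the port de bras is done on gameplay days. Textbox 2 names Assessment 7 after its instruments, sEMG and accelerometry, and not after a dance task. The description of the training hour mentions only setup and maximum contractions outside the game. On that reading the sensors record play and maximum efforts on those two days, and there is no extra rehearsal. This is possible but less natural, since the port de bras is the only movement described under Assessment 7. It limits the certainty of the point; it does not remove the need to clarify the sentence.

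The direction of any practice effect is also open to question in the CP group. The Background says that dystonic movements can worsen when movement is sustained. That stands: a gain is plausible, not shown. The one-day gap likewise rests on example schedules that are subject to change, with a tolerance of 1 week either way under Participant Timeline.

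Three stronger readings are tempting and are not supported.
- A reader might infer a contradiction with "The control groups will be assessed in the same schedule as the intervention groups". That sentence covers the assessment visits, which are shared; recordings on training days do not alter them.
- A reader might infer that the as-necessary qualifier makes the primary outcome optional. Outcomes separately requires the measures at all three time points, so this is loose wording.
- A reader might count five performances against three. That assumes one run per time point, which the protocol does not state.

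**Conclusion.** The point holds in limited form. Assessment 7 is scheduled on two days that only the intervention arm has. On the plain reading this means two more scheduled occasions of the primary-outcome task, the second on the day before post-assessment in both example schedules. Any resulting practice gain would be confounded with training in the intervention arm's before-after change and in any comparison with controls.

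Two things remain open: whether the port de bras is in fact performed on gameplay days, and how large a practice gain would be. The second cannot be derived from the documents, so the table of rejection rates shows sensitivity to an assumed gain and is not an estimate of bias. The case for acting rests on the remedy being cheap now and unavailable later, since the Results section says the trial has not started.

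**What to change.** Rewrite the timing sentence for Assessment 7 in Outcomes so that it states three things:
1. The port de bras is performed only at the baseline, post and 1-month assessments, and at each of them. This replaces the as-necessary qualifier for this task and matches the requirement already in that section.
2. The number of repetitions at each time point is the same in both arms.
3. On the first and last gameplay day, Assessment 7 is limited to sEMG and accelerometry during play and maximum efforts, without the port de bras. This also fits the existing description of the training hour.

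The cost is a short text edit and the loss of two intermediate kinematic recordings that have no control counterpart. If those recordings are wanted, the alternative is to equalise exposure by having controls perform the port de bras on two matching days, at the price of extra control visits.
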